#### Interim analyses

No interim analyses will be performed on collected data. Enrolment in the study will proceed sequentially, and each participant will immediately start administration of the assigned intervention, so data from each participant will be collected independently and even a partial dataset will not be available for interim analyses until the trial will be in an advanced stage of completion. No subgroup or other additional analyses will be performed. Non-adherent patients and dropouts will be excluded from the study and related data will not be collected.

The full protocol and used and/or analysed during the current study will be provided by the corresponding author upon request.

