#### Objectives

The aim of this pilot study protocol is to assess the feasibility of a randomised controlled trial to assess the effects of a 3-month probiotics therapy in a cohort of Parkinson’s disease patients. Specific feasibility objectives will be assessed to define the feasibility of the proposed clinical trial, including recruitment, acceptance and dropout rate, and outcome identification, as listed in the following Table 1.

**Table 1 Tab1:** Feasibility objectives

**Objective**	**Description**
Recruitment rate	The number of identified eligible subjects in a given amount of time, at the proposed clinical setting.
Acceptance rate	The fraction of identified eligible subjects who will be willing to participate in the proposed clinical trial.
Dropout rate and safety	Dropout rate will be reported as the fraction of enrolled subjects who will be dropped from the study for any reason. Reported reasons for subject drop-out will be recorded and analysed to confirm safety for both the treatment and placebo administration to enrolled subjects.
Primary outcome identification and sample size estimate	The primary outcome for the future main clinical trial will be identified among significant immune profile changes detected in the pilot trial. Data from the pilot trial will also be used to estimate an appropriate sample size for the main trial.
Secondary outcomes identification	Collected data in the pilot trial will be used to identify promising secondary outcome measures.

Data collected during this pilot study will include the following assessments to evaluate possible outcome measures for the definitive randomised controlled trial:1) Cytokines production (IFN-γ, TNF-α, IL-4, IL-10), as already tested in vitro, to confirm the immune-modulating potential of probiotics.2) Assessment of CD4+ and CD8+ T naïve/memory cells, CD4+ T helper subsets, CD4+ regulatory T cells, monocytes, and NK cells to test the immunomodulating effects of probiotics administration on the immune profile.3) Monitoring of motor and non-motor symptoms of PD, including gut function, and subjective quality of life during the trial period.

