### Eligibility criteria

All included patients will have a diagnosis of Parkinson’s disease with a disease duration between 2 and 5 years at baseline. Exclusion criteria for this study are listed in the following Table 2:

**Table 2 Tab2:** Exclusion criteria

**Condition**	**Exclusion criteria**
Present disease or disease history	Autoimmune disease Inflammatory bowel diseases Past major abdominal or pelvic surgery
Therapy	Immune-modulating or immunosuppressive Antibiotics therapy up to three months before enrolment
Feeding-related conditions	Usage of tube feeding Known or suspected allergy to any treatment or placebo component
Cognitive impairment	Known and established cognitive decline Any comorbidity preventing reliable completion of trial assessments
Parkinson’s symptoms	Motor fluctuations

Patients will be required to report any proposed modification in their medical therapy. Patients who will need substantial changes in antiparkinsonian therapy will be dropped from the trial. The use of laxative or prokinetic drugs will be recorded and is not an exclusion criterion per se, but the introduction of these medications or posology variations should be avoided during the trial.

Since the trial is primarily aimed at confirming the immunomodulating properties of probiotic treatment, any intercurrent and symptomatic infections, inflammatory episodes, or other medical conditions will be recorded. Evaluation by clinical staff for potential patient dropout will be based on the severity and temporal proximity of the event to scheduled visits and blood withdrawal. All participants will be advised to maintain a constant dietary intake and a regular physical activity during the trial. A daily report including quality of life aspects will be requested and evaluated using appropriate clinical scales. Informed consent will be obtained by clinicians after the eligibility assessment and during the first visit. All subjects or their legal representatives will be given all relevant information about the study structure and objectives. Additional consent will be requested for the use of collected data and biological specimens in ancillary studies.

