**Placebo composition**	
**Component**	**Quantity**
Maltodextrin	q.s.

Follow-up visits will be scheduled at 6 weeks after T0 (T1) and at 12 weeks after T0 (T2). At T1, physical and neurological examination will be repeated, and all clinical scales administered again, except for Bristol Stool Form Chart and MOCA. At T2, all assessments performed at T0 will be carried out again, including blood withdrawal.

Participants will be advised to report any suspected adverse reaction and new or worsening symptoms. Every report will be recorded, and a thorough evaluation will be performed by neurologists in the clinical staff in collaboration with the subject’s primary care doctor. Feedback will be provided to the participant as well as indications on continuing or stopping treatment administration. In accordance with the Declaration of Helsinki by the World Medical Association, every participant can freely request to be removed from the study at any moment. All participants will be requested to record daily treatment usage and keep empty packaging or unused doses for recollection after the trial completion. One courtesy call will be scheduled during treatment to reduce compliance issues. The use of immunomodulating drugs or antibiotic therapy is an exclusion criterion and patients starting such therapy during the trial period will be dropped from the study. Dose adjustments in antiparkinsonian therapy are permitted but should be avoided and substantial modifications to said therapies will cause dropping out from the study.

Every participant will be evaluated at enrolment by a clinical neurologist, who will assess needed adjustments in antiparkinsonian therapy that will be completed within two weeks from enrolment and before treatment administration to minimise the need for medical therapy modifications during the trial. The use of laxative or prokinetic drugs will be recorded and is not an exclusion criterion per se, but the introduction of these medications or posology variations should be avoided during the trial.

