### Outcomes

#### Primary feasibility outcomes

To assess the feasibility of the proposed clinical trial, we defined different feasibility objectives, as previously listed in Table 1.

More in detail, we will evaluate the potential recruitment rate for the clinical trial by recording the number of eligible outpatients who scheduled a neurological examination in the proposed clinical setting during the pilot trial. The acceptance rate will also be evaluated, by recording the fraction of identified eligible subjects who will be willing to participate in the proposed clinical trial. Both assessments together will allow for an initial estimate of the needed duration for the main clinical trial, once an appropriate sample size will be defined based on the pilot trial results. During the pilot trial, the dropout rate will also be recorded to adjust the predicted trial duration based on the fraction of dropped-out subjects during the trial period.

Reported reasons for subject drop-out will also be recorded and further analysed to confirm the safety of both the treatment and placebo administration to enrolled subjects. Collected data during the pilot trial will be analysed to assess whether a significant variation in any recorded parameter will occur between the two trial branches. This will allow to accordingly select one or more appropriate primary outcomes for the main trial, among collected immune profile data. Secondary outcomes for the main trial will be selected in the same way, among parameters who will show a remarkable variation.

More in detail, in our previous in vitro study (Magistrelli et al., 2019), we demonstrated that probiotics modulate ROS and cytokine production by driving an anti-inflammatory profile. Therefore, we will test whether these properties are confirmed in vivo. Particularly, in our study, we want to analyse whether probiotics may modulate cytokines production, such as IFN-γ, TNF-α, IL-4, IL-10, and ROS production.

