### Plans to promote participant retention and complete follow-up

Participants will be contacted by phone to timely schedule T1 and T2 visits. Any intercurrent health issue will be recorded and evaluated by clinical neurologists, who will assess the need to drop the subject from the study protocol. Any previously collected data will be kept after dropout and used as appropriate in statistical analyses.

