### Statistical methods

#### Statistical methods for outcome evaluation

To assess the main trial feasibility, the drop-out rate will be reported as the absolute number and percentage of total participants for both the intervention and placebo arms and will be accounted for when assessing an appropriate sample size for the main study. Feasibility will also be evaluated by recording all drop-out reasons and accordingly estimating an increase of the foreseen sample size.

Collected results will be reported as mean ± standard deviation (SD) of the mean, or median ± 25th and 75th percentile, as appropriate, and *n*, with *n* indicating the number of observations. The normality of data distribution will be analysed by means of D’Agostino-Pearson omnibus normality test. Mann–Whitney *U* test, Wilcoxon test, and Kruskal-Wallis tests will be used to assess differences in the distribution of non-parametric data. Paired and unpaired *t* tests will be used, as appropriate, to compare means and standard deviations for parametric data in the two treatment groups. Wilcoxon signed ranks test will be used to compare measures taken at T0 with the corresponding measures at T1 and T2 in the assessment of primary and secondary outcomes. When appropriate, efficacy outcomes will be reported as estimates with 95% confidence intervals. Statistical significance for correlations will be set at *p*<0.05. Commercial software (GraphPad Prism version 9.3.0 for Windows, GraphPad Software, San Diego, CA, USA, www.graphpad.com) will be used for data analyses and graph plotting.

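### Dropouts and non-adherent patients are excluded after randomisation and their data not collected, which conflicts with the protocol's own retention and reporting rules and leaves a completer comparison

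*Protocol article*

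**What the plan says.** The rule sits at the end of the Interim analyses section of the protocol article: "Non-adherent patients and dropouts will be excluded from the study and related data will not be collected". The same paragraph rules out subgroup and other additional analyses.

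Other sections treat the same patients differently:

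- **Retention and follow-up:** "Any previously collected data will be kept after dropout and used as appropriate in statistical analyses".
- **Statistical methods for outcome evaluation:** "the drop-out rate will be reported as the absolute number and percentage of total participants for both the intervention and placebo arms", and "Feasibility will also be evaluated by recording all drop-out reasons".
- **Objectives (Table 1):** "Reported reasons for subject drop-out will be recorded and analysed to confirm safety for both the treatment and placebo administration to enrolled subjects". Primary feasibility outcomes repeats this.

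The events that lead to removal after randomisation are in two places. Interventions (text after Table 3) says of immunomodulating drugs and antibiotics that "patients starting such therapy during the trial period will be dropped from the study". It also drops patients with substantial changes in antiparkinsonian therapy, as does Eligibility criteria. For intercurrent infections, inflammatory episodes and other conditions, Eligibility criteria leaves the decision to staff: "Evaluation by clinical staff for potential patient dropout will be based on the severity and temporal proximity of the event to scheduled visits" and to the blood draw.

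**The concern.** Two things are at stake.

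First, the sections cannot all be followed. An analyst holding T0 and T1 data from a patient who left at week 8 is told in one place to use them and in another that the patient is excluded. Staff are told to record why patients leave, and also that data related to those patients will not be collected.

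Second, the exclusions happen after randomisation, for reasons tied to the outcome. Antibiotics, immunomodulators, infections and inflammatory episodes all bear on plasma cytokines, ROS production and immune cell counts. The arms also differ in composition: the active sachet contains three bacterial strains and 2500 mg of fructo-oligosaccharides, and the placebo is maltodextrin only. Unequal tolerability or adherence is therefore possible. If removals differ between arms, patients who complete in one arm are no longer comparable with those who complete in the other. The main trial's primary outcome is to be picked from the immune changes found significant here, so a false signal would carry forward.

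**Working it through.** **1. The rules side by side**

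| Question | Interim analyses | Elsewhere |
|---|---|---|
| Data collected before dropout | Patient excluded from the study | Kept and used as appropriate (retention section) |
| Number and reasons for dropout | Related data not collected | Number by arm and all reasons required (Objectives, Primary feasibility outcomes, Statistical methods) |
| Non-adherent patients | Excluded, data not collected | Retention section is silent on them; Interventions collects usage records and returned sachets |
| T1 and T2 data after dropout | Not collected | No section provides for them |

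Reading the sentence as no further collection after dropout removes the clash over data already in hand. It does not remove the exclusion from analysis or the loss of later follow-up.

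**2. The plan's own figure**

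Sample size claims power above 80% for most cytokines with 80 subjects at a 0.05 threshold. No effect size, SD or test is given, so this cannot be reproduced. Taking 40 per arm, two-sided 0.05 and 80% power, the detectable between-arm difference is (1.960 + 0.842) × √(2/40) = 0.63 SD. The point here does not depend on this figure.

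**3. Bias from outcome-related removal**

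The document gives no dropout rate, so every input in this step is an assumption. Let the outcome be standard normal with no true effect. Remove a fraction q of an arm, namely those highest on a variable that has correlation ρ with the outcome. The mean of those left shifts by −ρ × φ(z)/(1 − q), where z is the (1 − q) normal quantile. The factor φ(z)/(1 − q) is:

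- q = 0.05: 0.109
- q = 0.10: 0.195
- q = 0.15: 0.274
- q = 0.20: 0.350
- q = 0.30: 0.497

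The between-arm bias is ρ times the difference of the two factors. At 20% versus 5% that is 0.350 − 0.109 = 0.241, so 0.3 × 0.241 = 0.07 SD and 0.8 × 0.241 = 0.19 SD. A simulation (40,000 runs, 40 randomised per arm, t test at 0.05) agreed with the formula and gave the type I error:

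| Removed, arm A vs arm B | Bias in SD, ρ = 0.3 / 0.5 / 0.8 | Type I error, ρ = 0.3 / 0.5 / 0.8 |
|---|---|---|
| 10% vs 10% | 0 / 0 / 0 | 5.1% / 4.9% / 4.9% |
| 20% vs 10% | 0.05 / 0.08 / 0.12 | 5.4% / 6.3% / 9.0% |
| 20% vs 5% | 0.07 / 0.12 / 0.19 | 6.0% / 8.0% / 13.7% |
| 30% vs 10% | 0.09 / 0.15 / 0.24 | 6.5% / 9.7% / 18.6% |

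The extreme case removes exactly the top 15% of one arm and nobody from the other (ρ = 1), which gives 0.27 SD. For scale, the smallest observed difference that reaches p < 0.05 with 40 per arm is 1.991 × √(2/40) = 0.45 SD.

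**4. Safety**

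For an event with an assumed 5% risk, the chance of seeing at least one case in 40 patients is 1 − 0.95^40 = 87%. If half of those events led to dropout and went unrecorded, it would be 1 − 0.975^40 = 64%. That loss arises only if the exclusion sentence overrides the adverse-event sections. Separately, and whatever is done about dropouts, 0 events in 40 leaves an exact two-sided 95% upper limit of 1 − 0.025^(1/40) = 8.8%.

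**The case against.** The strongest reply is that this is an exploratory pilot with feasibility outcomes, that the retention section already keeps dropout data, and that one loosely worded sentence should not be read as overriding the rest. Part of this stands, and it limits the point in five ways.

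- **Reach of the contradiction.** A reader might infer that the protocol promises to keep non-adherent patients' data and then discards them. It does not: the retention rule names dropouts only, and only data already collected.
- **Safety.** A reader might infer that adverse events in dropouts go unrecorded. Interventions, Blinding, and Adverse event reporting and harms each provide for recording reports or events. The safety plan is contradictory rather than absent.
- **Sensitivity analyses.** A reader might infer that the bar on additional analyses forbids them. The sentence does not mention them, and they are commonly left to an analysis plan that is not shown.
- **Dropout rate.** Withdrawals and imposed removals are pooled in the definition, but because reasons are recorded they can be separated.
- **Size.** The 0.27 SD figure needs perfect selection in one arm only. Equal rates with the same mechanism give no bias, and blinding limits biased staff judgement.

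Exploratory status does not dispose of the rest. The abstract names cytokines and ROS as the primary endpoint, the arms are compared with significance tests, and the result steers the main trial. Blinding does not prevent removals that the treatment itself causes or averts.

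**Conclusion.** The concern holds in limited form. For dropouts, the exclusion sentence conflicts with the retention rule and, read literally, with the requirement to report dropout numbers and reasons. For non-adherent patients, it is an exclusion after randomisation. Because several drop triggers are related to the immune outcomes, following the plan as written gives a completer comparison that randomisation does not protect.

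The size cannot be derived from the document. Under the assumptions above it ranges from no bias (equal rates and mechanism) through 0.07 to 0.19 SD with type I error of about 6% to 14% (20% versus 5%, correlation 0.3 to 0.8). It reaches 0.27 SD only in the extreme one-arm case. The documents support neither the extreme case as the expected one nor the conclusion that safety data are lost.

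**What to change.** Replace the sentence under Interim analyses and reconcile it with Eligibility criteria, Interventions, the retention section and Statistical methods. Deleting it alone is not enough, because the drop rules in the first two would still end follow-up.

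1. State that being dropped does not end data collection: participants who consent are still asked for T1 and T2 assessments, including T2 blood. This concerns data only. Which events should stop treatment is not at issue here.
2. Make the main between-arm comparison in all randomised participants with available T2 data, as randomised. Label the adherent or completer analysis a sensitivity analysis, with its criteria fixed before the code is broken.
3. Report dropout by arm, separating participant-initiated withdrawal from removal imposed by protocol or staff. Inflate the main trial for whichever types its own rules will produce; using voluntary withdrawal alone would undersize it if imposed removals remain.
4. Report adverse events by arm in everyone who took at least one dose, and undertake to describe safety rather than confirm it.

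The cost is wording, a few extra visits and blood draws, and a possibly diluted estimate. The main comparison would still be an available-case analysis. With 40 subjects already recruited when the article was written, any T2 blood already missed cannot be recovered, so the change is best made early.

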### Oversight and monitoring

#### Composition of the coordinating centre and trial steering committee

Trial management on a day-to-day basis will be carried out by clinical staff at the coordinating centre and by staff at the Center for Research in Medical Pharmacology. Neurological and clinical assessment, enrolment, and data collection will be performed by neurologists, postgraduate students in neurology, and medical students at the trial centre. Postgraduate students in Clinical Pharmacology and Toxicology and staff at the Center for Research in Medical Pharmacology will receive collected data and manage data storage at the University of Insubria, where data analysis will be performed by academic staff.

The trial steering committee will include academic staff from the University of Insubria and the University of Piemonte Orientale, who will monitor recruitment and timely data collection, oversee results reporting and publication. The committee will meet on a regular basis to monitor the regular course of the trial and ensure successful completion.

#### Composition of the data monitoring committee, its role, and reporting structure

The institutional review board explicitly approved the described trial protocol, for which the appointment of a Data Monitoring Committee was not requested, as no interim analyses will be performed besides subjective questionnaires. Appropriate safety monitoring will be performed directly on a per-subject basis by clinical staff. Furthermore, this pilot study protocol specifically excludes subjects with unstable or critical clinical conditions, and treatment with placebo or probiotics, during a relatively short period, is not expected to interfere with currently prescribed medical therapies.

#### Adverse event reporting and harms

All potential adverse events will be recorded by clinical staff and participants will be encouraged to report any new or worsening symptom, which will timely and thoroughly be evaluated for possible correlations with the administered treatment.

#### Frequency and plans for auditing trial conduct

No auditing will be performed for this trial.

#### Plans for communicating important protocol amendments to relevant parties (e.g., trial participants, ethical committees)

No protocol modifications are planned within the trial. Possible amendments will be communicated to the local ethics committee before the enrolment of participants.

## Discussion

The involvement of the immune system in the development and progression of Parkinson’s disease makes it a promising target for a disease-modifying therapy. This clinical trial will test the ability of probiotics therapy in modulating the peripheral immune system, which in turn is expected to have beneficial effects on disease progression and patients’ quality of life. If this trial shows a potential beneficial role of probiotics in immunomodulating peripheral immunity in PD patients, a trial with a larger cohort could be designed and disease progression could be monitored over a longer period to assess the disease-modifying potential of this intervention.

The possibility to use probiotics as adjuvant therapy in Parkinson’s disease could also help in reducing necessary drugs for the treatment of disease-related symptoms such as laxatives, prokinetics, and others (with a final reduction of individual therapy undesired effects and costs). The results of this study will also point further research in a disease-modifying direction. If further research shows a potential disease-modifying effect of probiotics, treatment could be proposed to all PD patients without any specific risks and increasing the quality of life in these patients.

In our mono-centric setting and considering rigorous exclusion criteria, one possible problem will be the recruitment of a large enough number of subjects. Enrolment will therefore be proposed to all eligible subjects by clinical neurologists during routine visits and given their recorded consent to receive information about ongoing research and recruiting trials. This will help in reaching the maximum number of possible participants, while ensuring strict adherence to inclusion/exclusion criteria, since participation will be only proposed to eligible patients by their neurologist and after a thorough medical evaluation.

All participants will be contacted during the trial to assess adherence to the assigned treatment and prevent dropouts whenever possible. Considering the current pandemic by SARS-CoV-2 and related vaccination campaigns, we will also record the vaccination status of all participants, so as to identify any possible interactions with clinical and laboratory data gathered for this trial. Since every participant will start the trial in a different time frame, we plan to schedule each participant’s agenda to minimise interactions with possible vaccine administrations or medical therapy variations. Such information will be gathered and, if needed, used at the best of our possibilities to assess potential biases in randomisation or data analyses.

